## Abstract

**Purpose:**

Genetic and lifestyle/environmental factors as well as their interplay contribute to the pathogenesis of type 2 diabetes (T2D). Several trials have shown that lifestyle intervention is effective in the prevention of T2D, but there are no trials that have taken into account the genetic risk of the participants. The aim of our T2D-GENE trial (ClinicalTrials.gov ID: NCT02709057) is to investigate the effects of lifestyle intervention on the prevention of T2D in participants with a high genetic risk of T2D compared with participants with a low genetic risk of T2D.

**Methods:**

Both intervention and control groups include 300 participants with low and 300 participants with high genetic risk for T2D. Genetic risk was evaluated by genetic risk score, and these two groups were matched additionally for fasting plasma glucose concentration, age, and body mass index. Corresponding control groups (300 participants each) do not have lifestyle intervention. The inclusion criteria are impaired fasting glucose at entry with or without impaired glucose tolerance, age 50–75 years, and body mass index ≥25 kg/m^2^. The primary outcome is incident T2D and the intervention lasts for 3 years.

**Conclusion:**

If the effects of the lifestyle intervention are independent from the genetic risk of the participants, our study will be of great importance for the entire T2D research community, health care providers, and individuals at high risk for T2D. In this case, lifestyle intervention is beneficial for all individuals at risk for developing T2D, independently of genetic risk.

**ClinicalTrials.gov ID:**

NCT02709057 March 15, 2016

The prevalence of diabetes mellitus will likely increase globally from 463 million individuals in 2019 to 700 million individuals in 2045 (1). This epidemic is mainly attributable to type 2 diabetes mellitus (T2D), which represents about 90–95% of all cases. T2D is a metabolic disorder characterized by chronic hyperglycemia and defects in insulin secretion, insulin action, or both. Genetic and lifestyle/environmental factors as well as their interplay contribute to the pathogenesis of T2D. Genome-wide association studies have identified so far >400 variants for T2D (2, 3). Almost all genetic variants regulate insulin secretion, and only a few of them regulate insulin sensitivity.

Several studies have indicated that lifestyle intervention is effective in the prevention of T2D. The first two of these randomized intervention studies, the Finnish Diabetes Prevention Study (Finnish DPS) and the Diabetes Prevention Program (DPP) from the USA (4, 5), showed that lifestyle intervention lowered the risk of T2D by 58% compared with the control group. In the Finnish DPS study (4), only people with impaired glucose tolerance (IGT) were included, and in the DPP study, people with both impaired fasting glucose (IFG) and IGT were accepted as entry criteria (5). Isolated IFG is a prediabetic condition where only fasting glucose is elevated caused by increased gluconeogenesis. Additionally, beta cell function is impaired, and glucagon secretion is inappropriately elevated (6). In contrast, people with combined IFG and IGT have a combination of increased gluconeogenesis, lack of suppression of glycogenolysis by insulin, impaired glucose disposal with extrahepatic insulin resistance, and impaired insulin secretion (7).

Several diabetes prevention trials have been published on the effects of lifestyle changes (diet and physical activity), and a meta-analysis of these trials reported a 57% reduction in incident T2D (8). There are no previous trials investigating the effect of the genetic background of the participants (the number of the risk alleles for T2D) on the effect of the prevention of T2D. Therefore, the aim of the T2D-GENE trial is to investigate the effects of lifestyle intervention (diet, physical activity, and weight maintenance/weight loss) on the prevention of incident T2D and the worsening of hyperglycemia in people with a high number of T2D risk alleles compared with people with a low number of T2D risk alleles. The second aim of our study is to investigate whether a group-based intervention utilizing a website is as effective as is an individual-based intervention. The hypotheses of the study are that lifestyle intervention is efficient independent of the number of T2D risk alleles (high and low genetic risks of T2D), and that a group-based intervention is as effective as an individual-based intervention in the prevention of T2D.

The primary outcome of our study is incident T2D defined by fasting plasma glucose ≥7.0 mmol/l or 2-h glucose ≥11.1 mmol/l in an oral glucose tolerance test (OGTT) or HbA1c ≥ 47 mmol/mol (6.5%), according to the American Diabetes Association criteria (9), or drug treatment for T2D started during a 3-year intervention trial. The secondary outcomes are changes in glucose area under the curve (AUC) in an OGTT, changes in insulin secretion and insulin sensitivity, and incident cardiovascular disease (CVD) events (fatal or non-fatal myocardial infarction, fatal or non-fatal stroke, death from cardiovascular causes or incident heart failure).

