## Participants and methods

### Participants

Study participants have been selected from the Metabolic Syndrome in Men (METSIM) study, which includes 10,197 men, aged from 45 to 73 years at baseline, randomly selected from the population register of the Kuopio town (baseline examination in 2005–2010) (10). The aim of the METSIM study is to investigate genetic and non-genetic factors associated with the risk of T2D, CVD, and insulin resistance-related traits.

The *inclusion criteria* for the present study were 1) IFG at entry (fasting plasma glucose 5.6–6.9 mmol/l) and with (2-h glucose 7.8–11.0 mmol/l) or without IGT (2-h glucose <7.8 mmol/l), and HbA1c <48 mmol/mol (<6.5%), 2) age 50–75 years, 3) body mass index (BMI) ≥25 kg/m^2^, and 4) the genetic risk score (GRS) (low risk 1–2 quintiles of the GRS and high risk 4–5 quintiles of the GRS). The *exclusion criteria* were 1) age <50 years or >75 years, 2) BMI <25 kg/m^2^, 3) type 1 or type 2 diabetes or isolated IGT (2-h plasma glucose <5.6 mmol/l and 2-h plasma glucose 7.8–11.0 mmol/l) or HbA1c ≥48 mmol/mol (≥6.5%), and 4) chronic diseases preventing to participate in the trial. After the identification of potential participants of the METSIM study, they were approached by an invitation letter.

The GRS in the present study was calculated on the basis of the number of risk alleles of 76 genetic variants increasing the risk for T2D as previously published (11). During the planning phase of the present study, less than 100 genetic variants increasing the risk for T2D had been published. A total of 600 participants were recruited and divided into two intervention groups (Fig. 1). Study participants, laboratory personnel, and clinical nutritionists were blinded with respect to the GRS of the participants throughout the study.

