**Fig. 1 F0001:**
[figure not shown]
Study design of the T2D-GENE trial. Participants in the intervention and control groups of the trial are divided into two groups based on the genetic risk score for type 2 diabetes (low genetic risk and high genetic risk). IFG, impaired fasting glucose; IGT, impaired glucose tolerance. The duration of the intervention is follow-up time is 3 years for all participants.

For both intervention groups (low GRS and high GRS), control groups of 300 participants (altogether 600 participants) of the METSIM study were selected and matched for GRS, fasting plasma glucose concentration, age, and BMI (Fig. 1). The rationale for these two control groups is to compare the incidence of T2D during the intervention between the two intervention groups and the two control groups.

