## Discussion

Our study will be the first study to compare the effect of lifestyle intervention on the prevention of incident T2D and the worsening of hyperglycemia in people with high genetic risk of T2D compared with people with low genetic risk of T2D.

If the effects of the lifestyle intervention are independent from the genetic risk of the participants, the implications of our study will be of great importance for the entire T2D research community, health care providers, and individuals at high risk for T2D. In this case, lifestyle intervention is beneficial for all individuals at risk for developing T2D, independently of genetic risk. If the effects of lifestyle intervention depend on the genetic risk, then individualized intervention programs are needed based on the GRS in people at high risk for T2D.

Due to the high number of people at risk for T2D in most countries, it will be challenging to organize individualized lifestyle counseling. In our study, lifestyle counseling is group-based, and a special website designed for this study is used for nutritionists-participant and participant-nutritionists contacts. From the resources point of view, it is important to examine whether a group-based intervention is effective similarly to a personal lifestyle counselling, and this study is likely to give an answer to this important question.

There are several previous lifestyle intervention studies, in counseling which the efficacy of lifestyle intervention on the prevention of T2D has been reported. Most of these studies have been performed in participants with IGT. In the present study, participants with IFG with or without IGT have been included. Most of the studies have combined diet and physical exercise, and a minority of the studies have only dietary intervention (17). In the systematic review and meta-analysis, the risk ratio (RR) was 0.68 (95% CI 0.5; 0.84) for dietary interventions and 0.59 (0.51; 0.69) for interventions combining diet and physical activity (17). In a more recent SRMA, the RR was 0.53 (0.41; 0.67) for interventions combining diet and physical activity (18).

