In previous studies, the interventions have mainly been individual based. In the Finnish DPS, the participants met clinical nutritionist seven times during the first year of the intervention and three times per year thereafter (4). In the DPP, the participants were contacted by phone (5). In real-world setting, a group-based approach has been studied. In an SRMA of real-world lifestyle modification aiming for T2D prevention, participants receiving group counseling by health care professionals had an RR of 0.67 (0.49; 0.92) as compared with control participants (19).

The most significant challenge of our study is that the group-based intervention utilizing a specific website is not efficient enough. However, due to an increasing number of people with impaired glucose metabolism or T2D, it is important to test this type of intervention since individual counseling is usually not possible, not at the present time and even less in the future, since the number of people at risk for T2D is increasing.

The results of the present study will reveal whether a lifestyle intervention (diet, physical activity, and weight maintenance/weight loss) is as effective in the prevention of incident T2D and the worsening of hyperglycemia in people with high number of T2D risk alleles compared with people with low number of T2D risk alleles, and whether a group-based intervention utilizing a website designed for this purpose is as effective as an individual-based intervention.

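### The second aim and hypothesis, that group-based is as effective as individual-based intervention, cannot be tested within this trial because no group receives an individual-based programme

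*Protocol article*

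**What the plan says.** The introduction gives the second aim: "The second aim of our study is to investigate whether a group-based intervention utilizing a website is as effective as is an individual-based intervention". It then lists as one of two hypotheses that "a group-based intervention is as effective as an individual-based intervention in the prevention of T2D". The Discussion returns to the question twice. It says that "this study is likely to give an answer to this important question", and its closing paragraph lists among the things the results will reveal "whether a group-based intervention utilizing a website designed for this purpose is as effective as an individual-based intervention".

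The design is described in the abstract, in Participants and in the Fig. 1 legend. On how the groups are formed, the legend says: "Participants in the intervention and control groups of the trial are divided into two groups based on the genetic risk score for type 2 diabetes". On the controls, the abstract says: "Corresponding control groups (300 participants each) do not have lifestyle intervention". The text after Fig. 1 gives the purpose of the control groups, which is to "compare the incidence of T2D during the intervention between the two intervention groups and the two control groups". The Intervention section describes one programme of group sessions plus a website for everyone in the intervention groups. Statistical analyses specifies a Cox model contrasting intervention with control in the low and high genetic risk groups.

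**The concern.** A claim that one mode of delivery is as effective as another needs both modes to be observed. Here one of the two is never delivered. A result against no intervention, however convincing, says whether the group programme works. It does not say whether it works as well as individual counselling.

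The Discussion presents the question as important for resources, because individual counselling is hard to organise for the large number of people at risk. If the aim stays as worded, a favourable result could be taken as support for replacing individual counselling, which the design cannot supply.

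**Working it through.** No figure in the article underlies the second aim, so there is none to reproduce. The check sets the groups against the comparison that the aim requires.

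**1. Groups and delivery mode** (Abstract; Participants; Fig. 1 legend; Intervention; Discussion)

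| Group | Genetic risk | Programme |
|---|---|---|
| Intervention, n = 300 | low | group sessions and website |
| Intervention, n = 300 | high | group sessions and website |
| Control, n = 300 | low | none |
| Control, n = 300 | high | none |

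The possible contrasts are intervention versus none, low versus high genetic risk, and their interaction. The number of individual-based groups is 0, so group-based versus individual-based cannot be estimated. The personal written feedback on food records (Diet) and the monthly website contacts (Intervention) are parts of the single programme. They do not form a separate arm.

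**2. What the sample size section assumes.** Calculation of the sample size takes 69/300 = 23% incidence in controls and 31/300 = 10% with intervention, from the Finnish DPS. The difference is 23% − 10% = 13 points. It then grants that the group programme may be less efficient than the individual approach of that trial, and works with an effect of 6%, described as about half. Read as percentage points:

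- cases prevented per 300 at the Finnish DPS effect: 69 − 31 = 38
- cases prevented per 300 at the planning effect: 0.06 × 300 = 18, leaving 69 − 18 = 51 cases
- ratio: 18/38 = 0.47

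A true effect of that size would count as a success against control while being about half the individual-based benchmark. Success on the planned comparison is therefore compatible with the second hypothesis being false. Whether the stated sample sizes are themselves correct is a separate matter and is not used here.

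**3. Precision of this trial's side of an indirect comparison.** Use SE(log HR) ≈ √(1/d₁ + 1/d₂), with 95% limits equal to the estimate times or divided by exp(1.96 × SE).

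| Events, intervention vs control | SE | Factor |
|---|---|---|
| 31 vs 69 (one stratum) | √(1/31 + 1/69) = 0.216 | 1.53 |
| 62 vs 138 (both strata, same rates in each) | √(1/62 + 1/138) = 0.153 | 1.35 |
| 51 vs 69 (one stratum, planning effect) | √(1/51 + 1/69) = 0.185 | 1.44 |

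An external trial's own error, and the differences between trials, come on top.

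**4. Comparability with the published trials**

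- *Population.* The introduction says the Finnish DPS enrolled only people with IGT. This trial requires IFG, accepts IFG with or without IGT, and excludes isolated IGT. It draws only on men aged 50–75 from one town's cohort. There is some overlap: the DPP accepted people with both IFG and IGT, and this trial includes people with both.
- *Controls.* The introduction calls the Finnish DPS and the DPP randomised. Here the controls were selected from METSIM and matched for genetic risk score, fasting glucose, age and BMI.

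**The case against.** The best defence is that the authors mean an indirect comparison. The sample size section uses the Finnish DPS as a benchmark, and the Discussion sets the trial beside individual-based trials and a pooled risk ratio of 0.67 for group counselling. On that reading the fault is one of wording: the question could stay if it were labelled indirect.

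Part of this stands. A descriptive comparison with published results is legitimate and worth keeping. But the article never says that the second aim is indirect, and such a comparison could not support the hypothesis as worded, given the differences in population and in how controls were obtained.

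It is also fair to say that this is a secondary aim, absent from the purpose and conclusion of the abstract, and that the primary outcome and the Cox analysis do not depend on it. That limits the severity.

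Three stronger inferences are tempting and are not supported:

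- *That the plan is at fault for having no equivalence margin or analysis for this aim.* The article condenses a full protocol, and an analysis plan may exist. Either could hold those items. Neither could supply a missing arm, and the point rests only on that.
- *That a significant result against no intervention will be reported as equivalence.* No text says so. The Discussion names the possibility that the group programme is not efficient enough as the study's most significant challenge.
- *That 31 versus 69 events is the most favourable case for precision.* It is not. The planning effect, with 51 versus 69 events, gives tighter limits (1.44 against 1.53), and pooling the strata gives 1.35. These figures only illustrate the limits of an indirect comparison. They do not establish the point.

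**Conclusion.** The point holds. The second aim and hypothesis cannot be tested within this trial, because no group receives an individual-based programme and the only internal contrast on delivery is group-based versus none. This follows from the stated arms and needs no numerical assumption. The sample size section reinforces it by allowing for about half the individual-based effect, if 6% is read as percentage points.

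The precision factors of 1.53 per stratum and 1.35 pooled assume the plan's own event counts, equal rates in both strata and no loss to follow-up.

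The question of whether the intervention effect depends on genetic risk is untouched. This is a should-fix to the trial's stated conclusions and gives no reason to doubt its primary comparison.

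**What to change.** - Restate the second aim and hypothesis as whether the group-based, website-supported intervention reduces incident T2D compared with no intervention.
- Disclose this as a change made after recruitment. The Time table section puts the end of recruitment at April 2018 and the first completions at April 2019, so no arm can now be added.
- Remove the claim of equal effectiveness with an individual-based intervention from the introduction and the Discussion, and remove the Discussion's statement that the study is likely to answer the question.
- Present any comparison with published individual-based trials as indirect and descriptive, and state beside it the differences in population and in how controls were allocated.
- If precision is shown, give the limits as the estimate times or divided by about 1.53 per stratum or 1.35 pooled, at 31 versus 69 events per stratum.

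The cost is rewording plus an open record of a late change to a stated hypothesis. The restated aim largely overlaps with the intervention-versus-control contrast already in the Cox analysis, so no new data are needed. The sponsor gives up a claim that the design cannot deliver.

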## Methods

### Study visits

Participants in the intervention groups have four laboratory visits (0, 1, 2, and 3 years), and participants in the control groups have two laboratory visits (0 and 3 years) (Fig. 2). The study visits at 0 and 3 years include a questionnaire on physical activity at work and leisure time, smoking, alcohol use, history of diseases, and current medication, and dietary habits (food frequency questionnaire), blood pressure (three measurements 1 min apart), body weight, height, and bioimpedance for measure fat percentage. Laboratory measurements include an OGTT (plasma glucose and insulin concentrations at 0, 30, and 120 min), HbA1c, and concentrations of total LDL and HDL cholesterol, total triglycerides, alanine aminotransferase, creatinine, interleukin 1 receptor antagonist, and high sensitivity C-reactive protein. The three-factor eating questionnaire R18 (TFEQ-R18) (12) is used for the evaluation of participants’ eating behavior (cognitive restraint, uncontrolled eating, and emotional eating) during the intervention. In the intervention group, the 1-year visit includes measurement of non-fasting HbA1c. At the 2-year visit, the TFEQ-R18 questionnaire is filled, and body weight, blood pressure, and the laboratory measurements are performed similarly as at 0-year and 3-year visits.

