### Baseline data

The baseline characteristics of the participants in the intervention groups are presented in Table 2 (low and high genetic risk groups combined). The mean age of the participants was 65.0±5.9 years (mean ± SD) at the baseline, and they were obese with the mean waist circumference higher than recommended. Fasting plasma glucose concentration was within the range of IFG (5.6–6.9 mmol/l), 2-h glucose concentration <11.1 mmol/l, and HbA1c (<48 mmol/l or <6.5 %). Blood pressure and concentrations of total and LDL cholesterol were slightly higher than recommended.

**Table 2 T0002:** Baseline characteristics of the participants in the intervention group (*n* = 635)

Variables	Range	Mean ± SD
Age, years	51–75	65.0±5.9
Body mass index, kg/m^2^	25.0–48.5	28.7±3.2
Waist circumference, cm	84.0–149.0	103.3±9.0
Systolic blood pressure, mmHg	101–193	134±15
Diastolic blood pressure, mmHg	60–117	84±9
Fasting glucose, mmol/l	5.6–6.9	6.0±0.3
2-h glucose, mmol/l	2.7–10.9	6.3±1.6
HbA1c, mmol/mol	29–45	37.5±3.1
Total cholesterol, mmol/l	2.49–7.91	5.03±1.00
Low density lipoprotein-cholesterol, mmol/l	1.05–5.88	3.10±0.90
high density lipoprotein-cholesterol, mmol/l	0.60–2.80	1.38±0.36
Total triglycerides, mmol/l	0.46–5.73	1.37±0.67

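### The primary outcome equates 6.5% HbA1c with 47 mmol/mol, while the entry criteria and baseline text equate it with 48, so a follow-up value of 47 has two classifications

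*Protocol article*

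**What the plan says.** The last paragraph of the protocol article's introduction defines the primary outcome as incident type 2 diabetes. It can be met by fasting glucose, by 2-hour glucose, by HbA1c, or by starting drug treatment, and these are joined by "or". The HbA1c component reads "HbA1c ≥ 47 mmol/mol (6.5%), according to the American Diabetes Association criteria".

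Three other places give the 6.5% limit differently (each quote stops just before the percent sign):

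- Participants, inclusion criteria: "HbA1c <48 mmol/mol (<6.5"
- Participants, exclusion criteria: "HbA1c ≥48 mmol/mol (≥6.5"
- Baseline data: "HbA1c (<48 mmol/l or <6.5", where the unit is also misprinted

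Study visits sets out when HbA1c is measured. "In the intervention group, the 1-year visit includes measurement of non-fasting HbA1c"; at 2 years that group repeats the laboratory measurements of the 0- and 3-year visits. By contrast, "participants in the control groups have two laboratory visits (0 and 3 years").

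**The concern.** One percentage threshold carries two values in mmol/mol, and one of them sits in the primary outcome. Because any single component is enough, HbA1c alone can make a participant an event. An analyst who codes the outcome in mmol/mol as printed counts a value of 47. An analyst who works from the 6.5% label, using the pairing in the entry criteria, does not. The same protocol would then yield two event lists.

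The 1-year visit in the intervention groups is the most exposed. Non-fasting HbA1c is the only laboratory measurement listed for it and no glucose tolerance test is described, so the HbA1c cut-off decides any laboratory-based event at that visit. A reading of 47 there would also enter the Cox model early, and controls have no corresponding visit.

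**Working it through.** **1. The thresholds side by side**

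| Place in the protocol article | Use | mmol/mol | Percentage label |
|---|---|---|---|
| Introduction, primary outcome | event | ≥47 | 6.5% |
| Participants, inclusion | eligible | <48 | <6.5% |
| Participants, exclusion | not eligible | ≥48 | ≥6.5% |
| Baseline data | description of those enrolled | <48 (unit printed as mmol/l) | <6.5% |

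The conflict is the interval 47 ≤ HbA1c < 48, which in whole numbers is the single value 47. It satisfies both <48 (labelled below 6.5%) and ≥47 (labelled 6.5%). If one value X served as <X at entry and ≥X for the event, the overlap would vanish.

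**2. Did the overlap arise at entry?**

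Table 2 gives a baseline HbA1c range of 29–45 mmol/mol for the 635 intervention participants. The maximum is below 47, so none of them was in the overlap at entry. The article gives no baseline range for controls.

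**3. How many follow-up values would read exactly 47?**

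The article has no figure of its own to reproduce here; this is for scale only. Under a normal approximation, a recorded 47 covers 46.5 to 47.5, so

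P(47) = Φ((47.5 − mean)/SD) − Φ((46.5 − mean)/SD).

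*Table 2 distribution unchanged (mean 37.5, SD 3.1):*
- (46.5 − 37.5)/3.1 = 2.903 and (47.5 − 37.5)/3.1 = 3.226
- P = 0.99937 − 0.99815 = 0.0012, or 0.12%
- 300 × 0.0012 ≈ 0.4 per 300 per test

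*Assumed follow-up mean 38, SD 3.3:*
- z = 2.576 and 2.879; P = 0.9980 − 0.9950 = 0.0030
- 300 × 0.0030 ≈ 0.9 per 300 per test

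*Assumed follow-up mean 40, SD 3.8:*
- z = 1.711 and 1.974; P = 0.9758 − 0.9564 = 0.0194
- 300 × 0.0194 ≈ 5.8 per 300 per test

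A wider assumption (the mean rising by 1 to 3 mmol/mol, SD 3.1 to 4) gives about 0.9 to 8 per 300 per test. No follow-up mean or SD is in the document, so only the first figure rests on documented inputs, and even it assumes no change over time.

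For comparison, the sample size section expects 31 events per 300 with intervention and 69 per 300 in controls.

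**4. Number of HbA1c tests after baseline**

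Intervention groups: years 1, 2 and 3. Control groups: year 3 only. This is a count of tests. It is not a count of additional participants classified as events.

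**The case against.** The strongest reply is that this is probably a one-digit slip with little effect. The outcome definition itself names 6.5%, the other three statements agree on 48, and with the Table 2 distribution fewer than one participant per 300 per test is affected. The sample size calculation does not use the threshold. All of that is fair, and it limits the size of the point. It does not settle which number the event derivation will use, and that number decides the primary outcome.

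One could also try to reconcile the text by rounding, taking both 47 and 48 as 6.5% to one decimal. That fails on the article's own terms, because the entry criteria put 47 below 6.5%. The inconsistency is internal and needs no conversion formula.

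A reader might infer more than the document supports, in three ways:

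- **That participants already at the event threshold were enrolled.** The baseline maximum of 45 rules this out for the intervention group. For controls it is possible under the criteria but not shown.
- **That the extra events fall mostly on the intervention arm because it has three tests to one.** Repeated values in one man are correlated. A man at 47 in year 1 who later reaches 48 is an event under either cut-off, and only his event time moves. Both arms are tested at year 3, and if the intervention works, more controls than intervention participants could sit at 47. No net direction follows. Unequal testing is a separate matter that remains under any cut-off.
- **That about 6 per 300 will be misclassified.** That is the top of an assumed range. It is also an upper bound on reclassified participants per test, because everyone enters with impaired fasting glucose and some at 47 would qualify on glucose or drug treatment.

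**Conclusion.** The contradiction stands. The primary outcome and the entry criteria assign different mmol/mol values to 6.5%, and a follow-up value of 47 is an event under one and below the threshold under the other. The consequence is ambiguous event classification at follow-up; enrolment of existing cases is not shown.

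The likely size is small: about 0.4 per 300 per test if the Table 2 mean and SD persist, and about 1–6 per 300 per test if the follow-up mean is 38–40 and the SD 3.3–3.8. The second range is assumed, both use a normal approximation, and both are upper bounds on changed classifications. The cut-off can act unequally because the groups are tested at different times, but the direction of any net effect is not established. The point merits correction because it concerns the definition of the primary endpoint, even though the expected number of affected participants is low.

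**What to change.** Reconcile the primary outcome definition in the introduction with the criteria under Participants, so that one mmol/mol value stands for 6.5% both at entry and for the outcome. The predominant pairing in the article is 48 mmol/mol with 6.5%, and adopting it would change one number in the outcome definition. If 47 was intended for the outcome, state that explicitly and correct the 6.5% label beside it. In either case derive all events, at every visit and in every group, from the single stated value, and settle this before events are derived. The unit in the Baseline data text can be corrected at the same time. The cost is one number in the text and one line in the event-derivation code; no visit, measurement or sample size changes.
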